## 3. Methods

### 3.1. Study Design

This multicenter prospective study employs a paired cohort design with a non-randomized, single-blinded methodology, in which each participant acts as their own control. The paired design allows for more accurate within-subject comparisons, controlling for individual differences that could otherwise introduce bias. By having each participant act as their own control, we minimize confounding factors related to baseline characteristics, reducing the need for randomization. A randomized approach could introduce biases in patient expectations or compromise the practicality of using the application. The single-blind design, with outcome assessors blinded to the app’s recommendations, reduces assessment bias while maintaining practical feasibility. This design provides an optimal balance between minimizing confounding and ensuring the study’s practicality.

During wound assessments, investigators remain blinded to the application’s recommendations. None of the professionals participating in this study have access to patient information. This study will enroll adult patients undergoing abdominal surgery across multiple hospitals. This study involves the use of the RedScar© app (University of the Balearic Islands, Palma, Spain) on patients’ smartphones. Patients will complete a brief health questionnaire and upload a wound photograph to the app, which will provide recommendations based on the risk of infection detected. Simultaneously, an in-person wound assessment will be conducted by the investigator to compare results.

This study adheres to the 2015 guidelines established by the Standards for Reporting Diagnostic Accuracy Studies (STARD) initiative [20]. This ensures transparency and rigor in reporting diagnostic accuracy outcomes. The study’s design and protocol underwent a comprehensive review and received approval from the Research Ethics Committee of the Balearic Islands (CEI-IB) in 27 June 2023 under reference number IB 5087/22 PI. Informed consent will be obtained from all participants, guaranteeing patient confidentiality and data protection throughout this research. The study protocol was registered on ClinicalTrials.gov in 20 January 2025 under the identifier NCT06771726.

### 3.2. Sample Size and Recruitment

A minimum of 168 patients have been required to estimate the agreement between in-person and app-based evaluations for infection detection with a 95% confidence level and a precision of 0.12. The sample size has increased by 10% to account for potential patient loss, resulting in a total of 185 patients. The expected Kappa index is approximately 0.8, with an estimated infection prevalence of 15% (in-person) and 20% (app-based) based on our previous study. Sample size calculations were performed using Epidat 4.0 (Direccion Xeral de Innovación e Xestion da Saude Pública, Galicia, Spain).

Patients will be recruited by the investigators through hospital outpatient clinics and surgical departments.

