RedScar© is fully automated, providing infection risk assessments without clinician input. Its independence from human intervention enhances scalability and cost-effectiveness in postoperative telemonitoring [16]. Utilizing real-time image processing and interactive questionnaires, RedScar© enables continuous patient engagement and rapid infection detection, potentially lowering rates of severe complications and hospital readmissions [17]. Previous studies have demonstrated that telemonitoring in surgery is feasible and can reduce the need for outpatient care while improving patient experiences [17,18,19].

The RedScar© Pilot Study [17]: Phase I/IIa evaluated the application for detecting and monitoring potentially infected surgical wounds. Among the 47 patients included, 41 successfully completed both remote and in-person follow-ups. The RedScar© system achieved a sensitivity of 100% for SSI detection, with a specificity of 83.13%. Patient satisfaction with telemonitoring was notably high: 97.6% considered it cost-effective, 90.47% believed it helped prevent absenteeism from work or school, and 80.9% found it a convenient option. While this pilot study confirmed the safety and feasibility of telematic follow-up using RedScar©, the low incidence of wound infections highlights the need for a multicenter trial to validate these findings and ensure standardized implementation across different healthcare centers. Our research aims to continue developing RedScar© as a user-friendly, reproducible tool to assist patients in managing surgical wounds at home, thus optimizing available resources.

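### The 15%/20% positivity rates behind the sample size do not fit the pilot accuracy reported in the Introduction; at that accuracy and 15% prevalence, 168 patients give a kappa half-width of about 0.136, not 0.12

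*Protocol article*

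**What the plan says.** The protocol article, section 3.2, gives the only justification of the study size: "A minimum of 168 patients have been required to estimate the agreement between in-person and app-based evaluations", "with a 95% confidence level and a precision of 0.12". The planning inputs are: "The expected Kappa index is approximately 0.8, with an estimated infection prevalence of 15% (in-person) and 20% (app-based) based on our previous study". An allowance for losses follows: "The sample size has increased by 10% to account for potential patient loss, resulting in a total of 185 patients".

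The Introduction describes the pilot of the same app, in which 41 of 47 patients completed both remote and in-person follow-up: "The RedScar© system achieved a sensitivity of 100% for SSI detection, with a specificity of 83.13" per cent. It calls the pilot's incidence of wound infection low and gives no figure. Nothing in the article explains how the rates in section 3.2 were obtained from that pilot.

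**The concern.** A test's positive rate follows from its sensitivity, its specificity and the prevalence. With 100% sensitivity, the app-positive rate exceeds the true prevalence by the false positives alone, (1 − specificity) × (1 − prevalence). Section 3.2 allows an excess of 5 points at 15% prevalence; the pilot specificity produces about 14. The two sections therefore describe apps of different accuracy, although section 3.2 credits its rates to earlier work by the same group.

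At stake is the stated precision. The variance of kappa depends on the whole 2×2 table, so a table with more false positives gives a lower kappa and, here, a wider interval for the same number of patients.

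**Working it through.** **Inputs.** From section 3.2: kappa 0.8, in-person rate 0.15, app rate 0.20, 95% confidence (z = 1.96), half-width 0.12, n = 168, or 185 with losses. From the Introduction: sensitivity 1.00, specificity 0.8313. Assumption: pilot accuracy applies per patient.

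**Formulas.** Kappa k = (po − pe)/(1 − pe). Large-sample (Fleiss-Cohen-Everitt) variance per patient V = (A + B − C)/(1 − pe)², with
- A = Σ p_ii [1 − (p_i. + p_.i)(1 − k)]²
- B = (1 − k)² Σ_{i≠j} p_ij (p_.i + p_j.)²
- C = [k − pe(1 − k)]²

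Then n = z²V/h², and the half-width is h = z√(V/n).

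**Step 1: reproduce 168.**
- pe = 0.15 × 0.20 + 0.85 × 0.80 = 0.71; po = 0.71 + 0.8 × 0.29 = 0.942.
- Both positive: (0.942 − 1 + 0.15 + 0.20)/2 = 0.146. In-person positive only: 0.004. App positive only: 0.054. Both negative: 0.796.
- V = (0.4836 + 0.0021 − 0.4330)/0.29² = 0.627.
- n = 1.96² × 0.6274/0.12² = 167.4, rounded up to **168**. The half-width at 168 is 0.1198.

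**Step 2: accuracy implied by the planning inputs.**
- Sensitivity = 0.146/0.15 = 97.3%; specificity = 0.796/0.85 = **93.6%**.
- Without using kappa: 100% sensitivity with 15%/20% needs specificity 1 − 0.05/0.85 = 94.1%.
- Keeping 15%/20% with specificity 83.13% forces sensitivity to (0.20 − 0.85 × 0.1687)/0.15 = 37.7%, and kappa to 0.18.

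**Step 3: pilot accuracy at 15% prevalence.**
- App-positive = 0.15 + 0.85 × 0.1687 = **29.3%**.
- Cells 0.15, 0, 0.1434, 0.7066; po = 0.8566; pe = 0.6446; k = 0.2120/0.3554 = **0.597**.
- V = (0.1989 + 0.0171 − 0.1132)/0.3554² = 0.814.
- Half-width **0.136** at 168 and **0.130** at 185. A half-width of 0.12 needs n = 217.2, so 218 evaluable patients.

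**Step 4: range over prevalence at pilot accuracy.**

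| Prevalence | App-positive | Kappa | Half-width at 168 | n for 0.12 |
|---|---|---|---|---|
| 20% | 33.5% | 0.66 | 0.121 | 172 |
| 15% | 29.3% | 0.60 | 0.136 | 218 |
| 10.1% | 25.3% | 0.50 | 0.155 | 281 |
| 5% | 21.0% | 0.33 | 0.172 | 346 |

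The 10.1% row is the top of the general incidence range cited in the Introduction; 5% and 20% are illustrative assumptions. A 20% app-positive rate would correspond to a prevalence of (0.20 − 0.1687)/0.8313 = 3.8%.

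**Step 5: dependence on the variance formula.** The simpler variance po(1 − po)/(1 − pe)² gives 174 for the stated inputs and 260 for pilot accuracy at 15%, so the direction of the result does not depend on the choice of formula.

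**The case against.** - **There is no calculation error.** This stands: 168 follows from the stated inputs. A reader might infer that 168 patients cannot deliver 0.12 at all. The documents do not support that; the shortfall arises only if the app performs as it did in the pilot.
- **The attribution is partly open.** The reference to the previous study follows the 15%/20% rates directly, and whether it also covers kappa 0.8 is grammatically unclear. No citation is attached, so identifying that study with the pilot is likely but inferred. The conflict does not need kappa, because the rates alone disagree with 100% and 83.13%.
- **The wrong input may be 15%, not 20%.** With 100% sensitivity and 83.13% specificity, 20% app-positive fits a prevalence of about 3.8%, and the pilot's incidence is called low. The documents do not settle which figure is off, so 29% and 0.60 are one resolution among several.
- **The unit is uncertain and the pilot small.** 83.13% equals 69/83, more than the 41 completers, which suggests assessments rather than patients (an inference). The exact 95% interval for 69/83 is 73.3% to 90.5%. At its upper limit kappa is 0.74, the half-width 0.128 and n = 191. Read instead as 34/41, the upper limit is 92.8%, where 168 would suffice. That is the favourable extreme of the pilot evidence rather than its estimate.
- **A new cut-off could raise specificity.** Section 2.1 plans to look for an optimal Red Proportion cut-off. That is a possible justification, but section 3.2 does not offer it.
- **No conclusion turns on kappa reaching 0.8.** This stands. A reader might infer that a study merely repeating the pilot would look like a failure. The article sets no kappa threshold, and section 2.1 makes sensitivity, specificity and the ROC curve the primary objective.

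**Conclusion.** The point holds as an inconsistency between stated figures. The 15%/20% pair, with or without kappa 0.8, needs a specificity of about 94%, roughly 10 points above the reported pilot value, and no passage reconciles the two.

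The precision shortfall rests on three assumptions: pilot accuracy is repeated, it applies per patient, and prevalence is 15%. Under these the loss is moderate, 0.136 against 0.12, and the allowance for losses does not recover it even if all 185 patients are evaluable. Lower prevalence makes it worse; 20% prevalence nearly removes the loss of precision, though kappa would still be 0.66. The larger discrepancy is in the expected kappa, about 0.60 rather than 0.8.

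Because these inputs are the only basis given for the size and precision, they should be corrected. Because the effect is conditional and moderate, and no decision rule depends on kappa, this is a should-fix point.

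**What to change.** Rewrite the inputs in section 3.2 in one of two ways.

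1. State one set of sensitivity, specificity and prevalence, derive kappa and the app-positive rate from it, and restate the expected precision for 168 evaluable patients. At pilot accuracy and 15% prevalence, that is kappa about 0.60, app-positive about 29% and a half-width of about 0.14. If the pilot prevalence differs from 15%, give it and use the figures that follow.
2. Keep 15%, 20% and 0.8, say that a specificity of about 94% is assumed, justify it, and stop attributing the 15%/20% pair to the pilot.

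Either way, say whether the pilot specificity counts patients or assessments.

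The cost is wording only. No added enrolment is required; under the first option the stated precision becomes slightly less favourable. Holding to 0.12 at pilot accuracy and 15% prevalence would instead take 218 evaluable patients, which is the sponsor's choice and not needed to remove the inconsistency.

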### 3.3. Inclusion Criteria

The inclusion criteria require participants to have signed an informed consent form, be over 18 years of age, and have undergone either urgent or scheduled surgery performed via laparotomy or laparoscopy. Additionally, participants need access to a smartphone capable of downloading the app, with either the patient or a close family member being able to operate it effectively. Patients also must be able to attend follow-up consultations at the surgical outpatient clinic after discharge, one-week post-surgery, or earlier if the app flags a potential infection.

### 3.4. Exclusion Criteria

The exclusion criteria encompassed patients who lacked access to a smartphone or were unable to properly use the app, such as those unfamiliar with mobile devices or unable to comprehend the app’s functionality or questions. Patients who did not provide informed consent or who were unable to comply with the follow-up requirements were also excluded from this study.

### 3.5. Withdrawal Criteria

Patients may withdraw from this study at any time for any reason, and the reasons for withdrawal will be documented in the Case Report Form (CRF). These reasons may include the withdrawal of consent, the investigator’s discretion, or intercurrent illnesses that may compromise safety or interfere with this study. Once a patient has withdrawn, they will not be replaced or re-enrolled in this study.

### 3.6. Visit Schedule

The patient will be discharged after surgery when deemed appropriate by the attending physician.

They must download the RedScar© app before discharge so they can be taught how to use it correctly, and any questions regarding the app’s questionnaire will be addressed. Detailed explanations will be provided about changes in the wound, such as swelling, increased temperature, etc. As stated earlier, the inability to understand these conditions or use the app is a reason for exclusion.

The patient will attend their first follow-up at the surgical outpatient clinic on day 5 post-surgery to assess the wound and again on day 8 to remove staples and check the wound’s condition. Prior to the consultation, the patient will need to take a photograph of the wound using the app (on postoperative days 5 and 8) so the app’s results can be compared with the investigator’s in-person evaluation (Figure 1).

If a wound infection is suspected, the patient will need to visit the outpatient clinic or hospital emergency department (depending on the investigator’s guidelines) to be assessed by the main investigators or, if unavailable, by the attending nurse. They will confirm the presence or absence of wound infection, document it in the patient’s medical record, and perform the initial treatment. Additionally, the patient will be given a conventional follow-up appointment with the surgery clinic, as is performed for patients not included in this study.

At the end of the follow-up, patient satisfaction will be evaluated using the Telemedicine Satisfaction Questionnaire (Table 1) developed and validated by Yip et al. [2], which has been used in similar studies [17,18].

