### 5.4. Structure of Personal Information

Patient information will be stored in a JSON format, utilizing a key-value system. Researchers will also have accounts within the same system, each with a unique identifier that links them to the patients they are associated with. Furthermore, multiple researchers may be linked to a single patient.

As for the account parameters, the ENABLED_ACCOUNT parameter allows remote control of the user’s account status in case they cease collaboration. Regarding the images, the same principle applies as with the researchers: it is a list of image-type objects, and there will be as many as the patient has chosen to upload. The two permissions mentioned previously will also apply.

Although it has been mentioned multiple times, it is worth reiterating that all key-value information in the JSON file is encrypted.

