**Figure 3 jcm-14-02210-f003:**
[figure not shown]
Examples of images that are expected to be included in this study, taken by patients in the preliminary phase of this study (see the RedScar© Pilot Study [15]).

**Table 1 jcm-14-02210-t001:** Satisfaction questionnaire [2].

Satisfaction Questionnaire	Answer
1. The information received before participating in this study was adequate.	Yes/No
2. I do not have difficulties with the questionnaire used within the application.	Yes/No
3. I do not have difficulties when taking the photo and uploading it to the mobile application.	Yes/No
4. I have spent less time with telematic follow-up than with personal revision.	Yes/No
5. I think that telematic follow-up is cheaper than the personal revision.	Yes/No
6. I think that telematic review could prevent absenteeism from work/school.	Yes/No
7. Telematic follow-up seems more comfortable to me than follow-up in consultations.	Yes/No
8. I think that telematic monitoring could detect a bad evolution earlier.	Yes/No
9. I think the healthcare provided via telemedicine is consistent.	Yes/No
10. The care received seems adequate to me.	Yes/No
11. Overall, I am satisfied with the quality of service being provided via telemedicine.	Yes/No
12. I would prefer telematic follow-up to face-to-face consultations.	Yes/No
13. I will use telemedicine services again.	Yes/No
14. Following the instructions of the application, have you checked your wound at your health center?	Yes/No, Why?
15. Although the application had ruled out the infection of the wound, have you preferred to check it in person?	Yes/No, Why?
16. Despite using the application, have you consulted any other source (Google-type web search, opinion of close relatives)?	Yes/No, Why?
17. How do you think we can improve the RedScar© application? Leave your comment.	

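### No app entry is required at unscheduled visits for suspected infection, so the app's sensitivity may be biased upward

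*Protocol article*

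**What the plan says.** The primary objective (section 2.1) is the sensitivity and specificity of the app against in-person diagnosis, so each infected patient needs an app verdict and a clinical verdict on the same wound state.

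Section 3.6 sets the required app entries. Before the consultation, "the patient will need to take a photograph of the wound using the app (on postoperative days 5 and 8"; the stated purpose is "so the app’s results can be compared with the investigator’s in-person evaluation".

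The next paragraph of section 3.6 opens a second route to the reference diagnosis: "If a wound infection is suspected, the patient will need to visit the outpatient clinic or hospital emergency department". Of the staff there it says: "They will confirm the presence or absence of wound infection, document it in the patient’s medical record, and perform the initial treatment". It requires no app entry on this route and does not say who or what raises the suspicion.

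Three other places bear on the point:
- Section 3.3 foresees attendance "or earlier if the app flags a potential infection".
- Section 5.4 allows extra images: "there will be as many as the patient has chosen to upload".
- Item 15 of the satisfaction questionnaire (Table 1) asks: "Although the application had ruled out the infection of the wound, have you preferred to check it in person".

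**The concern.** The two kinds of early infection are treated unequally. If the app prompts the visit, a positive app result exists by construction and can be matched with the clinic's confirmation. If the patient, a relative or another clinician raises the suspicion, no app reading need exist at the time of diagnosis. The next required entry then shows a wound that has already been diagnosed and treated, so it cannot stand in for the missing reading.

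The availability of the index test among infected patients therefore depends partly on the index test's own result. If the infections without a reading are ones the app detects less often, the reported sensitivity is too high. The pilot reported 100% (section 1), and a similar result here could not be told apart from one in which a few misses were never read. An analysis plan can state how such cases are scored, but it cannot recover a reading that was not taken before treatment.

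**Working it through.** **1. The plan's own figure.** Inputs from section 3.2: kappa 0.8, prevalence 15% in person and 20% by app, precision 0.12 (taken as a half-width), 95% confidence.
- Chance agreement: 0.15 × 0.20 + 0.85 × 0.80 = 0.71. Observed agreement: 0.8 × (1 − 0.71) + 0.71 = 0.942.
- Cell positive on both: (0.942 − 1 + 0.15 + 0.20) / 2 = 0.146. The others are 0.004 (in-person positive only), 0.054 (app positive only) and 0.796.
- With the Fleiss-Cohen-Everitt large-sample variance of kappa, n = 1.96² × V / 0.12² = 167.4, rounded up to 168. The stated minimum is reproduced.
- 168 × 1.10 = 184.8, rounded up to 185, as stated.
- Sensitivity implied by these inputs: 0.146 / 0.15 = 97.3%.

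**2. Expected infections.** 0.15 × 168 = 25.2, so about 25 (0.15 × 185 = 27.75 if nobody is lost). One infection in 25 is 4 percentage points.

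**3. Which app result exists, by route to diagnosis.**

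| Route | Required app result before diagnosis |
|---|---|
| Found at the day-5 or day-8 consultation | Yes, paired |
| Early visit because the app flagged | Positive result exists |
| Other suspicion, before day 5 | None required; a voluntary upload may exist |
| Other suspicion, between days 5 and 8 | Only the day-5 entry, possibly of an earlier wound state; a voluntary upload may exist |

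**4. Size of the possible bias.** Let u of the 25 infections be unscored, S the sensitivity among those scored, and q the proportion of the unscored that the app would have detected. Sensitivity over all 25 is [S × (25 − u) + q × u] / 25, so

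reported minus all-patient value = (u / 25) × (S − q).

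The documents give neither u nor q. Both are assumptions, shown as ranges. The worst case, q = 0, is:

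| u | If 100% is reported | If 97.3% is reported |
|---|---|---|
| 1 | 24/25 = 96% | 93.4% |
| 2 | 23/25 = 92% | 89.5% |
| 3 | 22/25 = 88% | 85.7% |
| 4 | 21/25 = 84% | 81.8% |
| 5 | 20/25 = 80% | 77.9% |

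For u = 3, the Wilson 95% interval for 22/25 is 70% to 96%. At a far end of u = 8, the worst case is 17/25 = 68% against a reported 17/17.

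Other values of q change the answer:
- q = S: the difference is zero, and the only loss is in the number of cases.
- u = 3, S = 100%, q = 50%: 3/25 × 0.5 = 6 points.
- u = 5 with 18 of 20 scored infections detected: 90% is reported, and the value over all 25 lies between 18/25 = 72% and 23/25 = 92%. The error can therefore go slightly the other way.

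**The case against.** The strongest reply is that the unpaired route may be narrow. The only trigger for an early visit named in section 3.3 is an app flag, and the suspicion in section 3.6 could be read as one raised by the app or at a paired consultation. Section 3.1 describes app use and in-person assessment as simultaneous, without naming days. Patients may upload when they wish, and item 15 of Table 1 foresees someone attending after a negative app result, who could be scored as a miss. The app's own questionnaire asks about the symptoms that would bring a patient in, so it might well have flagged such wounds. Scoring rules commonly sit in an analysis plan, which section 4.2 says will be prepared before the database is closed. The flow chart, not visible here, may also show the unscheduled route.

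Much of this stands. A reader might infer that these infections have no app result at all, that they are probably misses, and that they drop out of the estimate. The documents support none of the three. An earlier or voluntary entry may exist; an infection on which the app was not used has not been shown to be a miss; and no section says how such cases are counted.

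What the reply does not remove is the collection rule itself. Section 3.6 does not restrict suspicion to the app, and patients are taught before discharge to recognise wound changes. Voluntary uploads leave the availability of the reading to the patient's choice.

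**Conclusion.** The point holds as a weakness of the visit schedule, with a possible rather than demonstrated bias. The required app entries are fixed at days 5 and 8, while infections may also be confirmed and treated at visits where no concurrent entry is required. App-flagged early infections always carry a positive result; others may not carry a result that can be used.

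The effect is about 4 points of sensitivity for each unscored infection that the app would have missed, given about 25 expected infections. Three such cases would turn 88% into a reported 100%. That figure assumes the planned 15% prevalence, that the cases are left unscored, and that the app would have missed all three. The percentages in the q = 0 table are worst-case bounds, not expected effects.

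It would also go too far to conclude that every infection without a reading should count as not detected in the main estimate. That would treat missing readings as false negatives and move the target from the accuracy of the app to the yield of the whole follow-up programme, which section 2.1 does not ask for.

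**What to change.** In section 3.6, ask the patient to complete the app questionnaire and photograph before any in-person assessment for suspected infection, whoever raised the suspicion, where this does not delay care. Keep the result hidden from the assessor, and record in the CRF what triggered the visit.

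State the pairing rule: an infection confirmed at an unscheduled visit is paired with that pre-examination verdict and not with a later entry made after treatment. Where no verdict exists before diagnosis, report the number of such infections and give best-case and worst-case bounds on sensitivity as a sensitivity analysis. Do not count them as not detected in the main estimate.

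The cost is a sentence in the visit schedule and patient instructions, one CRF item and one pairing rule. The downside is a few minutes of app use before an unscheduled visit and a possibly lower reported sensitivity. Some urgent visits will still lack an entry, which is why the bounds are needed.

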Several studies have explored the use of mobile applications for the telematic detection of SSIs. Some applications utilize thermal cameras to identify increases in temperature associated with infections [10], while others employ dressings monitored via mobile apps to detect or prevent infections at early stages [11]. However, these technologies are often complex and not widely applicable outside of research settings. The emergence of artificial intelligence (AI) and machine learning algorithms has opened new possibilities for SSI detection, with studies reporting predictive capabilities even before clinical symptoms appear [12]. Despite this progress, challenges related to cost, accessibility, and implementation hinder widespread adoption in clinical settings [12]

The RedScar© application v1.9 (Compilation 23) (University of the Balearic Islands, Palma, Spain) is designed to operate simply using a patient’s mobile phone and an internet connection, offering advantages over existing applications. Unlike previous studies that require the external evaluation of wound images [13].

The RedScar© app employs a comprehensive approach to assess surgical wound infections by integrating patient-reported data with automated image analysis. The user-friendly interface includes a structured questionnaire covering key wound-related factors such as pain severity (measured via a visual analog scale, VAS), redness, burning sensation, wound leakage, swelling, liquid secretion, and fever. Patients must complete all questions before proceeding to the next step, which involves uploading a wound photograph. Once submitted, the app initiates a multistep computerized image analysis process based on fuzzy sets and gray-scale mathematical morphology [14] which is then extended to color images [15]. By combining image analysis with questionnaire responses, RedScar© autonomously generates a diagnosis without requiring direct supervision from healthcare professionals. Developed in Java SE 11 (Oracle, Austin, TX, USA) using the Android Studio environment, RedScar© integrates advanced image-processing techniques through Python-based (Python 3.7, Python Software Foundation, Wilmington, DE, USA) repositories which localizes surgical staples and the wound in an image and reconstructs images.

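### Day-8 app results recorded after a positive in-person diagnosis are not independent of the reference test, yet the protocol compares both days without separating them, which can bias sensitivity in either direction

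*Protocol article*

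**What the plan says.** All references are to the protocol article.

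- **Test order (section 3.6).** "The patient will attend their first follow-up at the surgical outpatient clinic on day 5 post-surgery to assess the wound and again on day 8". The photograph is taken before each consultation, "on postoperative days 5 and 8) so the app’s results can be compared with the investigator’s in-person evaluation". Both days are comparison points, and no exception is made for a patient diagnosed at the first.
- **What happens when infection is suspected (section 3.6).** The patient is seen in person by the main investigators or, failing that, the attending nurse: "They will confirm the presence or absence of wound infection, document it in the patient’s medical record, and perform the initial treatment". Section 3.3 also provides for an earlier visit when the app raises a flag.
- **What the app result is made of (section 1).** "Patients must complete all questions before proceeding to the next step, which involves uploading a wound photograph". The questions cover pain, redness, burning, leakage, swelling, secretion and fever. "By combining image analysis with questionnaire responses, RedScar© autonomously generates a diagnosis".
- **Who is blinded (section 3.1).** "The single-blind design, with outcome assessors blinded to the app’s recommendations". No blinding in the other direction is described.
- **What is estimated (section 2.1).** Sensitivity and specificity of the app against in-person diagnosis, and a ROC analysis that chooses a cut-off for the Red Proportion. Neither is tied to a particular day.

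**The concern.** An accuracy study needs the index test to be made without knowledge of the reference result. Here that is protected in one direction only: the assessor does not see the app's output. On day 8 the patient supplies part of the index test after having been examined on day 5. If infection was found then, the entry also follows diagnosis and initial treatment. In the app's intended use, without clinician input, neither would have happened.

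Two routes lead from the first positive diagnosis to the day-8 app result:

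1. **Knowledge.** A patient who probably knows the wound is infected may report more symptoms. An infection the app missed on day 5 can then appear as an app-positive on day 8.
2. **Treatment.** A treated wound may be less red, so the app may turn negative while the investigator still classes the wound as infected.

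The first raises sensitivity and the second lowers it. The Red Proportion is an image measure, so its ROC curve and cut-off are exposed to treatment but not to what the patient knows. Handling repeated visits correctly for clustering would not help, because the app result itself has changed. What is at stake is the miss rate, the error that matters most for a tool meant to work without a clinician.

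**Working it through.** **1. The plan's own figure.** Section 3.2 gives kappa 0.8, prevalence 0.15 (in-person) and 0.20 (app), 95% confidence and precision 0.12.

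- Chance agreement: 0.15 × 0.20 + 0.85 × 0.80 = 0.71.
- Observed agreement: 0.8 × (1 − 0.71) + 0.71 = 0.942.
- Both positive: (0.942 − 1 + 0.15 + 0.20)/2 = 0.146. The other cells are 0.004 (app misses), 0.054 (app false positives) and 0.796 (both negative).
- Large-sample (Fleiss–Cohen–Everitt) variance of kappa times n: (0.4836 + 0.0021 − 0.4330)/(0.29²) = 0.627.
- n = 1.96² × 0.627/0.12² = 167.4, rounded up to **168**, as stated.

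The sample size reproduces and is not in question. The same table gives the accuracy the planning implies: sensitivity 0.146/0.15 = **0.973**, specificity 0.796/0.85 = 0.936.

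**2. Expected infections.** 168 × 0.15 = 25.2.

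**3. Upward route.** Assumed quantities, none given in the protocol:

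- s: true sensitivity of the app.
- f: share of infections already diagnosed on day 5 and still present on day 8, taken as 0.3 to 0.7.
- c: share of day-5 misses that turn app-positive on day 8 because of the verdict, taken as 0.5 to 1.
- Otherwise the day-8 app result equals the day-5 result.

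If every infected visit counts, there are (1 + f) infected visits per infected patient, and

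observed sensitivity = s + (1 − s) × f × c/(1 + f).

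If a patient counts as detected when any visit is app-positive,

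observed sensitivity = s + (1 − s) × f × c.

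| True s | Per visit, lowest to highest | Any positive visit, lowest to highest |
|---|---|---|
| 0.70 | 0.735–0.824 | 0.745–0.91 |
| 0.80 | 0.823–0.882 | 0.83–0.94 |
| 0.90 | 0.912–0.941 | 0.915–0.97 |

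Example for s = 0.80, f = 0.5, c = 1: per visit 0.80 + 0.20 × 0.5/1.5 = 0.867; any positive visit 0.80 + 0.20 × 0.5 = 0.90.

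At the implied s = 0.973, expected misses are 25.2 × 0.027 = 0.7. With f = 0.5 and c = 1 the gain is 0.027 × 0.5/1.5 = 0.009 per visit, or 0.027 × 0.5 = 0.013 for any positive visit: about 0.01. At the pilot's 100% it is nil.

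**4. Downward route.** Let d be the share of day-5 detections that turn app-negative on day 8 after treatment while still classed as infected. Per visit this subtracts s × f × d/(1 + f). The two routes cancel when s × d = (1 − s) × c. With s = 0.80 and c = 1 that is d = 0.20/0.80 = 0.25; above it, the net per-visit bias is downward. Under an any-positive rule this loss does not appear, because the day-5 positive is kept.

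**5. After the fix.** If each infected patient's pairs stop at the first positive in-person diagnosis, the extra (f) visits drop out, both terms vanish, and the expected estimate returns to s (0.80 in the example).

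**The case against.** The strongest reply is that the harm needs a counting rule the article does not contain. It does not say that visits are pooled, that any positive visit suffices, or that day 8 overwrites day 5. Section 4.2 leaves the analysis plan to be prepared before the database is closed, and a first-pair or censoring rule there would remove the problem. This stands in part: a miss *can* be scored as a detection, and nobody can say that it *will* be. But the test order and both comparison days are fixed in section 3.6 without distinction, so comparing both as written would count these pairs.

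Further points also stand. That the patient learns the verdict is inferred from a face-to-face visit with treatment; it is not stated. The sentence on confirmation and treatment belongs to the suspected-infection pathway, and the flow chart, which might show whether such patients still give a day-8 pair, is not available here. The weight of the patient's answers in the app's diagnosis is not given.

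A reader might infer that day-8 agreement is pushed upward in infected and uninfected patients alike. The document does not support that. Treatment may turn the app negative, and a patient told on day 5 that there is no infection might under-report a new one, which would lower sensitivity. A reader might also take an extreme count as typical: 25 infected, 3 missed on day 5, all 3 app-positive on day 8, so 25/25 = 100% instead of 22/25 = 88%. That is correct arithmetic on chosen inputs, with every miss converted.

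**Conclusion.** The concern holds in a limited form. App–clinic pairs taken after a positive in-person diagnosis are not independent of the reference test, and section 3.6 as written includes them. The bias in sensitivity can go either way. The upward part is up to 0.08 per visit (0.882 − 0.80) or 0.14 with any positive visit (0.94 − 0.80) if true sensitivity is 0.80 under the assumed ranges, and about 0.01 if it is the implied 0.973. Near-perfect sensitivity should not be taken for granted, since section 1 gives the pilot's low infection incidence as the reason for a larger trial. The documents do not support a claim that the results will be inflated, nor that the Red Proportion ROC is affected by what the patient knows.

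**What to change.** - State in sections 2.1 and 3.6 that app–clinic pairs count toward primary sensitivity and specificity, and toward the Red Proportion ROC, only up to and including the visit (scheduled or app-triggered) of the first positive in-person diagnosis.
- List later pairs separately. Do not let a later app-positive replace an app-negative at the diagnosing visit.
- Report day-5 and day-8 accuracy separately. Stopping at diagnosis does not remove any effect of the day-5 visit on patients told there was no infection, so the day-8 figures need to be visible on their own.

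This is a matter of wording and analysis. It needs no extra patients or visits and no change in care. The cost is a few fewer pairs and possibly a less favourable sensitivity.
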